## Abstract

**Background:**

Upper limb motor impairment is a common consequence of stroke, and the effectiveness and underlying mechanisms of rehabilitation therapy for improving upper limb function remain uncertain. Functional near-infrared spectroscopy, a reliable wearable neuroimaging technique, holds promise for investigating brain activity during functional tasks. This study aims to explore the synchronous oxygenation characteristics of the central cortex and upper-limb flexors during a grasping task and investigate the rehabilitation mechanisms of upper limb motor function in individuals with stroke.

**Methods:**

Participants with stroke who demonstrate the ability to grasp and lift cubic wood blocks of different sizes (2.5cm^3^, 5cm^3^, and 10cm^3^) using their affected hand will be divided into three groups: A, B, and C. Each group will consist of twenty stroke patients, resulting in a total of sixty participants with stroke. Additionally, twenty matched healthy subjects will be enrolled as a control group. Comprehensive assessments will be conducted before and after the intervention, including blood oxygen parameter monitoring of the cerebral cortex and upper limb flexors using fNIRS during the grasping task. Other assessments will include MyotonPRO, the Modified Ashworth Scale, the upper extremity section of the Fugl–Meyer Assessment, the Action Research Arm Test, and the Modified Barthel Index. The study will be undertaken between January 2024 and September 2025.

**Conclusions:**

The results of this trial will provide an in-depth understanding of the Characteristics of central cortex and upper-limb flexors synchronous oxygenation during grasping task and how it may relate to the rehabilitation mechanism of upper limb motor function in people with stroke.

**Clinical trial registration:**

https://www.chictr.org.cn, identifier ChiCTR2400080619.

## Introduction

Stroke, a leading cause of death and disability (GBD Stroke Collaborators, 2019; Stinear et al., 2020), poses a growing challenge due to the aging population and improved survival rates (Li, 2020). Studies have indicated that a significant proportion of stroke patients experience upper limb motor impairment, both in the acute and chronic stages of recovery (Grattan et al., 2019). This impairment directly affects patients’ quality of life and places a substantial economic burden on families and society.

Functional rehabilitation after stroke is believed to result from reorganization within the central nervous system. Understanding the relationship between these neurobiological changes and the recovery process is crucial for helping effective treatment approaches. Non-invasive techniques such as functional magnetic resonance imaging (fMRI), transcranial magnetic stimulation (TMS), and electroencephalography (EEG) have provided valuable insights into the functioning of the human brain (Ward, 2004). Previously, fMRI was employed to investigate intraregional activation and interregional connectivity during bilateral (antiphase and in-phase) and unilateral upper limb movements (Lin et al., 2017), while EEG was utilized to study cognitive anticipatory processes during palm grasping in subacute patients following stroke (Chen et al., 2018). However, these techniques have limitations, such as environmental requirements and human activity, which somewhat hinder the study of cortical activity during functional tasks. In this regard, near-infrared spectroscopy (NIRS) emerges as a novel and non-invasive functional neuroimaging technology. By indirectly assessing cerebral cortex and muscle tissue activity through the detection of blood oxygen parameters [Oxygenated Hemoglobin (HbO), Deoxygenated Hemoglobin (HbR), and Total Oxygenated Hemoglobin (HbT)] based on the neurovascular coupling mechanism, NIRS offers a promising method for investigating neurovascular activity during functional motor tasks. Unlike other techniques, NIRS imposes fewer physical and environmental restrictions and has minimal contraindications (Scholkmann et al., 2014), thereby facilitating the study of cortical activity characteristics in human functional activities.

Current research (Kasahara et al., 2011; Arnemann et al., 2015) in patients following stroke has focus on understanding how focal brain injuries affect brain networks and whether these changes are associated with functional recovery. However, the underlying mechanisms of functional recovery after stroke are still actively being investigated (Ward, 2004). Furthermore, there remains a notable discrepancy between clinical evaluation results and real-life functional abilities of patients (Greeley et al., 2021). To bridge this gap, there is a growing interest in portable neuroimaging techniques that can objectively measure the neurophysiology related to functional behavior (Greeley et al., 2021). Functional near infrared spectroscopy (fNIRS) is a validated and reliable neuroimaging technique that can be used as a wearable device during functional activities (Plichta et al., 2006). It has demonstrated high consistency with fMRI results in detecting cortical activities (Huppert et al., 2017). Some studies have utilized fNIRS to investigate sensorimotor stimulation of the affected hand in patients following stroke though median nerve electrical stimulation (Huo et al., 2019a). However, to date, there have been no reports on the neurophysiological activity of cerebral cortex function region detected by fNIRS during upper limb grasping function in patients following stroke.

While muscle NIRS technology has been widely used in laboratory and exercise settings to observe changes in muscle metabolism and oxygenation (Perrey and Ferrari, 2018), its application has primarily focus on athletes (Giovanelli et al., 2020), healthy people (Beever et al., 2020), and conditions such as cystic fibrosis (Werkman et al., 2016). There is currently a lack of studies utilizing NIRS to examine upper limb muscle hemodynamics in stroke patients, particularly during grasping tasks. Therefore, there is a need to investigate the immediate muscle hemodynamics of upper limb grasping tasks in stroke patients using NIRS, as this will provide valuable insights into the neurophysiological aspects of motor function recovery in this population.

Virtual reality (VR) training which can induce the active participation of patients and provide more repetitive training (Levin et al., 2015), has gained attention as a rehabilitation intervention for improving upper limb function and quality of life in patients following stroke (Lo et al., 2017a). While some studies have shown beneficial effects of VR training on upper limb motor function recovery, a multi-center randomized controlled trial using a commercial gaming system failed to demonstrate superiority over traditional occupational therapy (Saposnik et al., 2016). However, literature analysis suggests that VR systems providing task-based training can significantly enhance upper limb function in stroke patients (Lohse et al., 2014). Previous research combining VR training with conventional rehabilitation therapy in patients with cerebral infarction has shown long-lasting improvements in upper limb motor function (Laver et al., 2017). In our previous prospective clinical study on rehabilitation intervention of multi-sensory interactive training for patients with cerebral infarction, it was found that virtual reality training combined with conventional rehabilitation therapy could improve upper limb motor function of patients with cerebral infarction and the effect could last for 1 year (Lo et al., 2017a; Zhao et al., 2019c). With the increasing application of VR in stroke rehabilitation, understanding its impact on neuronal activity and motor function becomes crucial.

The primary objective of this study is to investigate the characteristics of oxygenation in the central cortex and upper-limb flexors during grasping tasks in individuals with stroke. fNIRS systems will be used to simultaneously assess blood flow dynamics in the central cortex and upper-limb flexors during grasping tasks, evaluating the heterogeneity of muscle oxygenation activity in the upper-limb flexors and analyzing the activation levels of cerebral cortex functional areas. The secondary objective is to explore the hemodynamic alterations in the cerebral cortex and flexor muscles of the affected upper limb during grasping tasks, induced by the combination of VR and conventional rehabilitation therapy, to attempt to investigate the rehabilitation mechanisms of upper limb motor function in individuals with stroke. Participants with stroke will undergo a combined intervention of VR training and conventional rehabilitation therapy. Changes of hemodynamic in cerebral cortex and upper limb flexor hemodynamics, as well as upper limb motor function, will be evaluated before and after the intervention. Furthermore, correlations between each parameter will be analyzed to gain insights into the relationship between VR training, neuronal activity, and upper limb motor function in stroke patients.

## Methods and design

### Study design

This study follows a longitudinal non-randomized controlled design to examine the synchronous oxygenation characteristics of the central cortex and upper-limb flexors during a grasping task in stroke patients with varying levels of grasp function.

### Study setting

The study is conducted at the Department of Rehabilitation Medicine, First Affiliated Hospital of Sun Yat-sen University in China. Participants are recruited from the inpatient ward, and all interventions are delivered within the Hospital Rehabilitation Department by the hospital staff.

### Recruitment

Eligible patients admitted to the inpatient ward are screened as part of routine assessment. The clinical team identifies suitable participants and provides them with written information about the study. A member of the research team then approaches the potential participants, explains the study further, and obtains written consent from those interested in participating. A screening log is maintained to record details of non-recruited patients and reasons for exclusion.

### Ethics

Data collection will be performed according to the World Medical Association Declaration of Helsinki. The study has received ethical approval from the Human Subjects Ethics Subcommittee of the First Affiliated Hospital of Sun Yat-sen University (Ethical approval number: [2022] 308). Additionally, the study is registered in the Chinese Clinical Trial Registry (Registration No.: ChiCTR2400080619, registered on 2 February 2024). Any significant modifications to the study protocol will be communicated to all relevant parties.

### Participants

Inclusion Criteria:

1.First stroke confirmed by CT or MRI.2.Medically stable.3.Age between 40 and 80 years.4.Onset of stroke occurred between two weeks to three months.5.Right handedness.6.No severe cognitive impairment (MMSE ≥ 22 points) and able to follow motor commands.7.Able to maintain an upright position in an armless seat for at least 30 min.8.Modified Ashworth grade of the affected upper limb is equal to or less than grade 2.9.Brunnstrom motor function grade of the affected hand is equal to or greater than grade 3, and able to grasp a 2.5cm3 wood block with effort.10.Patient and their family members agree to participate in the study and have signed the informed consent.

Exclusion Criteria:

1.Unstable clinical condition.2.Presence of any neuropsychiatric illness other than stroke.3.Diagnosis of schizophrenia, bipolar disorder, obsessive-compulsive disorder, personality disorder, or major depression.4.Presence of skin lesions or infections on the upper limb.5.History of upper limb fractures, deformities, or finger absence.

Sample Size:

Based on the sample size of previous studies (Huo et al., 2019a), a total of 60 patients following stroke will be enrolled in this study, with 20 patients in each of the three groups.

Group A: Patients who can only grasp and lift a 2.5 cm^3^ wooden block with their hemiplegic hand.Group B: Patients who can grasp and lift 2.5 cm^3^ and 5 cm^3^ blocks with their hemiplegic hand but cannot lift 10 cm^3^ blocks.Group C: Patients who can pick up 2.5 cm^3^, 5 cm^3^, and 10 cm^3^ wood blocks with their hemiplegic hand but exhibit abnormalities in speed and coordination during the task.

In addition, a control group of 20 age-matched healthy subjects without neurological diseases or history of upper limb trauma will also be enrolled.

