### Statistical analysis

Before conducting parametric tests, several steps were taken to prepare and analyze the data. Outliers were identified using normal Q–Q plots and box plots, and data points that were more than three standard deviations from the mean were considered outliers and subsequently excluded from the analysis (Minati et al., 2011). Missing values were addressed using multiple imputation analysis to estimate and replace the missing data points (Blankers et al., 2010).

Descriptive statistics were used to summarize the demographic and clinical characteristics of the study participants. The normality of the data distribution was assessed using the one-sample Kolmogorov-Smirnov test. For comparisons between different groups, chi-square tests were used for categorical variables, while independent t-tests were used for continuous variables.

To evaluate the differences in outcome measures before and after the intervention for participants with stroke, paired sample *t*-tests were employed. The correlations between variables were assessed using either the Pearson correlation coefficient (r) or the Spearman correlation coefficient (ρ), depending on the nature of the data.

The significance of interregional coupling strength between the resting state and different grasping states was evaluated using a one-way analysis of variance (ANOVA). Additionally, χ^2^ tests were utilized to identify statistically significant differences in interregional coupling direction between the resting state and different grasping states.

All statistical analyses were performed using SPSS software (version 20.0; SPSS Inc., Chicago, IL, USA). All tests were two-tailed, and a significance level of *p* < 0.05 was considered statistically significant.

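### Patients enter two weeks to three months after stroke, but the stated between-patient analyses ignore time since onset, so brain–function correlations may partly reflect recovery stage

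*Protocol article*

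**What the plan says.** All statements are in the protocol article.

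- **Entry window.** The inclusion criteria under Participants read: "Onset of stroke occurred between two weeks to three months". This is the only use made of time since onset.
- **Groups.** Study design states: "This study follows a longitudinal non-randomized controlled design". Under Participants, A, B and C are defined by the block sizes the affected hand can lift, and "a total of 60 patients following stroke will be enrolled in this study, with 20 patients in each of the three groups". The healthy comparison is "a control group of 20 age-matched healthy subjects".
- **Duration.** Experimental procedure gives every stroke participant three weeks of intervention, with assessments before and after.
- **Purpose of the correlations.** The objectives at the end of the Introduction say that "correlations between each parameter will be analyzed to gain insights into the relationship between VR training, neuronal activity, and upper limb motor function", within a secondary objective about rehabilitation mechanisms.
- **Methods.** Under Statistical analysis, for group comparisons, "chi-square tests were used for categorical variables, while independent t-tests were used for continuous variables". Pre–post differences use paired t-tests. For associations, "The correlations between variables were assessed using either the Pearson correlation coefficient (r) or the Spearman correlation coefficient". A one-way ANOVA and chi-square tests compare coupling between resting and grasping states. No covariate, stratum or partial correlation is named.

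**The concern.** Patients in one group can be at very different times after stroke. If both a haemodynamic measure and a motor score depend on that time, the two will correlate across patients even when neither acts on the other. The plan means to use such correlations to understand mechanism, and a simple coefficient cannot separate the two explanations.

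A related question arises for A, B and C. Nothing in the allocation balances time since onset across them, so a difference in oxygenation between grasp levels could also be a difference in recovery stage if the groups happen to differ in it.

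This is separate from whether change can be credited to VR training. It affects the between-patient results even if no treatment effect is claimed.

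**Working it through.** **Inputs from the protocol article.** Entry window 2 weeks to 3 months, taken as 14 to 90 days; 60 stroke patients, 20 per group; intervention 3 weeks; two-sided 0.05.

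**Window.** 90/14 = 6.4-fold. Its width is 90 − 14 = 76 days, and the three-week observation period is 21/76 = 28% of it.

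**The plan's own figure.** The 60 cannot be reproduced. It is justified as "Based on the sample size of previous studies", with no effect size, SD or power. The point does not depend on it.

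**Correlations.** Assumptions, none of them in the documents:

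- a brain or muscle measure X and a motor measure Y each correlate *a* with time since onset T;
- X and Y are unrelated given T;
- the three stroke groups are pooled (n = 60).

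The induced correlation is then r = a². By Fisher's z, the chance of a significant result is approximately

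P = Φ(√(n−3)·atanh(r) − 1.96) + Φ(−√(n−3)·atanh(r) − 1.96).

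Example, a = 0.6: r = 0.36, atanh(0.36) = 0.377, √57 = 7.550, product 2.846. Then 2.846 − 1.96 = 0.886 and Φ(0.886) = 0.81.

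A simulation (20,000 runs per value) tested the simple correlation on n − 2 = 58 degrees of freedom. It also tested the partial correlation (r_XY − r_XT·r_YT)/√((1 − r_XT²)(1 − r_YT²)) on 57.

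| a | induced r | simple, Fisher z | simple, simulated | partial, simulated |
|---|---|---|---|---|
| 0.2 | 0.04 | 6% | 5.8% | 5.1% |
| 0.3 | 0.09 | 10% | 10.6% | 5.0% |
| 0.4 | 0.16 | 23% | 23.3% | 4.8% |
| 0.5 | 0.25 | 49% | 48.6% | 5.1% |
| 0.6 | 0.36 | 81% | 82.1% | 5.3% |

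The two methods agree to about one percentage point. The article does not say whether groups are pooled. Within one group of 20, √17 = 4.123 replaces √57, and P falls to about 10% at a = 0.4 (4.123 × 0.161 = 0.665) and 34% at a = 0.6 (4.123 × 0.377 = 1.554).

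**Comparisons among A, B and C.** Take 20 v 20, no true group effect, outcome correlated *a* with T, and mean T differing by g SD. The induced difference is a·g SD. Simulated rates for the independent t-test:

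| a | g = 0 | g = 0.5 | g = 1 |
|---|---|---|---|
| 0.2 | 5.2% | 6.0% | 9.2% |
| 0.4 | 4.9% | 9.6% | 23.8% |
| 0.6 | 5.1% | 15.0% | 45.3% |

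With g = 0 the error rate stays at 5%. Spread in T within a group adds variance but does not bias the comparison.

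**Other analyses.** A paired t-test on mean change remains valid, and varying recovery only widens its interval. Rest v grasping, baseline v task and affected v unaffected hemisphere are compared within a person, so T is the same on both sides. Healthy controls have no onset date. None of these belongs to this point.

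**The case against.** **An article need not list covariates.** A fuller analysis plan, not shown, may add adjustment, and the planned summary of clinical characteristics could include time since onset. That is fair, and it limits the point to what is stated. But the article does name its methods, the correlations are simple ones, and reporting a baseline variable does not adjust for it.

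**Stronger reading: bias is certain because recovery slows steeply across this window.** A reader might infer this, but the documents say nothing about the shape of recovery. They also do not say how strongly any measure depends on time since onset, or whether A, B and C differ in it. At a = 0.2 the inflation is negligible. The documents support only that bias may occur.

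**Stronger reading: the primary objective is distorted.** This is not supported either. That objective is largely descriptive. Describing oxygenation at each grasp level needs no adjustment, and adjusting answers a different question. The unadjusted description should therefore stay.

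**Adjustment imposes a causal model.** The Introduction links functional recovery to central reorganisation. If time since onset affects function only through cortical change, it does not confound that link, and partialling it out removes real variation in the cortical measure. This stands as a reason to show both results. It does not favour the simple coefficient alone, which cannot tell the two cases apart.

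**Other prognostic factors, such as age (40 to 80), are also unadjusted.** True. Time since onset has the more direct claim because the study is about recovery, but it is not the only candidate.

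**Conclusion.** The point holds in limited form. The entry window is wide, the stroke groups are not randomised, and the stated between-patient analyses make no use of time since onset, although the correlations are meant to inform mechanism.

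For the pooled correlations, the chance of a significant result with no direct link runs from about 6% to about 81% as the assumed correlation with time since onset goes from 0.2 to 0.6. For A–C comparisons it runs from 6% to 15% if mean time since onset differs by 0.5 SD, from 9% to 45% if by 1 SD, and is 5% if it does not differ. These ranges rest on assumed values, and the documents do not show where in them the trial lies.

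This is a worthwhile improvement to a stated method. It does not invalidate the design.

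**What to change.** In Statistical analysis:

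1. Report days from stroke onset to first assessment, by group A, B and C (median, quartiles, range).
2. Beside each simple correlation among stroke patients, show the partial correlation, or a regression, adjusted for days since onset. Fix the scale (days or log days) before analysis.
3. Keep the unadjusted description of A, B and C, and show beside it the comparison with days since onset as a covariate.
4. State that a correlation will not be read as a rehabilitation mechanism if it disappears on adjustment. Judge this from the estimate and its confidence interval, not from a change in significance alone.
5. Leave the paired tests, the within-person comparisons and the healthy-control comparisons as they are on this point.

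Onset timing is already needed for eligibility, so no new data or patients are required. The cost is one degree of freedom (58 to 57 for a pooled correlation) and some wording.

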### Limitations

There were several important limitations in this study that warrant consideration. Firstly, the trial sample size was relatively small. A small sample size can impact the statistical power of the study and may limit the ability to draw robust and generalizable conclusions from the findings. Secondly, the study design employed a non-randomized clinical trial approach, and participants were recruited using convenience sampling from the inpatient population with stroke. This could limit the generalizability of the findings. Thirdly, the study primarily focused on the assessment of hemodynamic changes during grasping motor tasks. Consequently, the understanding of the intervention’s effects on overall motor function may be limited by this narrow focus on specific upper limb tasks. Lastly, the two functional near infrared spectroscopy detection systems was at different sampling rate during the measurements.

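### Healthy controls are matched on age only and the named between-group tests are unadjusted, so a sex imbalance could pass for a stroke effect in the patient-versus-healthy comparison

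*Protocol article*

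**What the plan says.** The abstract says that "twenty matched healthy subjects will be enrolled as a control group" and does not name the matching variables. The Participants section names one: "a control group of 20 age-matched healthy subjects without neurological diseases or history of upper limb trauma will also be enrolled". It also sets the patient numbers: "a total of 60 patients following stroke will be enrolled in this study, with 20 patients in each of the three groups". The eligibility list has an age range but no provision on sex.

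On sampling, the Limitations section says that "participants were recruited using convenience sampling from the inpatient population with stroke". The article does not say how the healthy subjects are found.

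On analysis, the Statistical analysis section says that for comparisons between groups "chi-square tests were used for categorical variables" and "independent t-tests were used for continuous variables". No covariate is named. The tests are two-sided at 0.05.

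The fNIRS data acquisition section has Group A grasp only the 2.5 cm³ block, Group B the two smaller blocks, and Group C and the controls all three. Every patient is tested with the unaffected hand and then the affected hand.

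**The concern.** Matching and adjustment are the two means of keeping a background variable out of a patient-versus-healthy comparison. Here the matching covers age alone, and the named test adjusts for nothing. If the inpatient sample has a different share of men from the controls, and if men and women differ in signal amplitude, part of that difference is counted as stroke.

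The healthy contrast matters to the trial. The primary objective is to characterise cortical and flexor oxygenation during grasping in stroke. The Discussion expects cortical activation to be altered, citing higher cognitive demands in patients than in healthy people. An amplitude difference produced by the sex mix would be read as such an alteration, or would hide one.

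The article gives no sex distribution and no sex effect on either signal. The concern is therefore about an open route for bias, not about a bias shown to be present.

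**Working it through.** **Inputs from the article.** 20 controls; 20 patients in each of three groups, 60 in all; independent t-test, two-sided, 0.05. The sample size is justified only as "Based on the sample size of previous studies", with no effect size, SD or power, so there is no planned figure to reproduce.

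**Inputs assumed.** Male share pS in patients and pC in controls, and a sex difference g in amplitude measured in within-sex SDs.

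**Step 1: what the design can detect.** At 80% power the detectable difference is (1.960 + 0.842) × √(1/n₁ + 1/n₂).
- 20 v 20: 2.802 × √(1/20 + 1/20) = 0.89 SD
- 60 v 20: 2.802 × √(1/60 + 1/20) = 0.72 SD

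**Step 2: spurious difference.** Bias = g × (pS − pC). At 70% v 40% men and g = 1.0 it is 1.0 × 0.30 = 0.30 SD, about a third of the detectable difference at 20 v 20 (0.30/0.89 = 0.34).

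**Step 3: false-positive rate of the unadjusted t-test with no true stroke effect** (simulation, 40,000 runs per case, sex counts held at the stated shares).

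| Men, patients v controls | g | Bias (SD) | 20 v 20 | 60 v 20 |
|---|---|---|---|---|
| 65% v 50% | 0.5 | 0.075 | 5.0% | 5.2% |
| 65% v 50% | 1.0 | 0.15 | 4.7% | 5.8% |
| 70% v 40% | 0.3 | 0.09 | 5.7% | 6.2% |
| 70% v 40% | 0.5 | 0.15 | 6.7% | 8.1% |
| 70% v 40% | 1.0 | 0.30 | 10.8% | 15.5% |
| 75% v 35% | 1.0 | 0.40 | 17.9% | 27.0% |

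If sex counts vary at random around a 40-point gap with g = 1.0, the rates are about 20% and 29%. Putting 0.40 straight into a t-test with a total SD of 1 gives 23% and 33%. That is too high when g is in within-sex units, because the sex difference also widens the spread inside each group. At 70% men and g = 1 the total SD is √(1 + 0.7 × 0.3) = 1.10.

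**Step 4: which comparison each column describes.** All 60 patients share only the 2.5 cm³ block. The 5 cm³ block allows at most 40 v 20 (Groups B and C), and the 10 cm³ block 20 v 20 (Group C). The article does not specify a pooled comparison.

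**Step 5: would a baseline check catch it?** A chi-square test would flag 70% v 40% men with power of 48% at 20 v 20 and 67% at 60 v 20. Even with identical source populations, a gap of 20 points or more arises in about 25–27% of 20 v 20 samples and 12–14% of 60 v 20 samples. Such chance gaps do not raise the long-run error rate, but they do distort the estimate in the trial that has one.

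**Step 6: after matching.** With 65% men in both groups the bias is zero. The unadjusted t-test then rejects 4.5% (g = 0.5) or 3.0% (g = 1.0) of the time at 20 v 20, slightly below 5% because the sex variation is still counted as noise.

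**The case against.** **Many of the planned contrasts are within patients.** The paired pre-post tests, a comparison of affected with unaffected hand, and the lateralization index each use the patient as their own reference. This stands and limits the point to the comparison with healthy subjects. A reader might infer that this comparison is how the trial tests its primary hypotheses. The article does not label them so, and it grounds the flexor hypothesis in weakness of the affected side, which the two-hand design can address within patients.

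**A reader might infer that the muscle outcome is affected most.** The article does not support this. It gives no sex effect on muscle or cortical signals and does not discuss how body composition or strength bears on amplitude. Cortical beta values and wavelet amplitudes enter the same kind of comparison.

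**The t-test sentence may describe baseline comparisons.** It sits in the paragraph on demographic and clinical summaries, and covariates are often left to an analysis plan that is not shown here. This has some force. But the article names no other test for comparing fNIRS amplitudes between patients and controls. The matching rule is also a recruitment decision, and a later covariate cannot restore overlap if the 20 controls are badly unbalanced.

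**A reader might see a contradiction between the abstract and the Participants section.** There is none. The abstract is shorthand for age matching, and no text promises matching on sex.

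**The harm may be negligible.** That is so for a small gap or a weak sex effect, and the article does not say which case applies.

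**Conclusion.** The point holds for the stroke-versus-healthy comparison of cortical and muscle fNIRS amplitudes, and for that comparison only. As written, neither the matching rule nor the named tests control for sex, and convenience sampling gives no assurance that the sex ratios agree.

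The size is conditional. With a small imbalance or a weak sex effect, the false-positive rate stays near 5–7%. With both a 30–40 point gap in male share and a sex effect near 1 within-sex SD, it is about 11–20% at 20 v 20, and about 15–29% if all 60 patients are pooled on the 2.5 cm³ block. Both inputs are assumptions. The article does not show that an imbalance exists or that either signal differs by sex. This is a worthwhile and inexpensive design correction, not evidence that the results will be wrong.

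**What to change.** 1. **Participants:** frequency-match the 20 controls to the stroke sample on sex as well as age, for example with the same sex ratio within age bands. This has to be settled before control enrolment is complete.
2. **Statistical analysis:** compare stroke groups with controls by a linear model with age and sex as covariates in place of the unadjusted t-test, and say which paragraph governs baseline description and which the outcome comparisons.
3. **Abstract:** name the matching variables.

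The cost is slightly slower recruitment of controls and two degrees of freedom. No treatment, visit or measurement changes. If control enrolment is already complete, the covariates can still be added, but they give less protection where the sex ratios barely overlap.
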